### 3.3. Randomization

Randomization is performed via an eCRF platform developed by PHARMASSIST CRO (Athens, Greece), which is also used to document all the study contacts, assessments and outcomes. 

Patients and researchers are aware of the treatment group that patients have been randomized to. The two antiarrhythmic drugs, amiodarone and flecainide, have different dosages and a different time and method of administration, making the design of a single or double-blinded trial design difficult in an Emergency Department setting. 

The process of active randomization in each of the two groups in a 1:1 ratio contributes to the prevention of selection bias and is undertaken by an independent authorized researcher who is not taking part in the rest of the trial’s procedures.

### 3.4. Sample Size

In our meta-analysis, we estimated the pooled cardioversion rate by flecainide within 4 h 65% whereas by amiodarone 23% (17). Taking 65% as our point estimate, the steering committee of FLECA-ED considers that flecainide can be regarded as non-inferior to amiodarone in patients with ischemic cardiomyopathy if the lower margin of the confidence interval does not go lower than the pooled rate (65%) by more than 20% (i.e., if it is not lower than 45%). Based on these assumptions, we expect that a sample size of 96 patients per arm is required to achieve 80% power to demonstrate the efficacy of flecainide in these patients, when a type I error rate is set at 0.05. Given the close follow-up of our patients in our registry, we do not expect a substantial dropout rate and thus aim to recruit a total of 200 (100 per arm) patients.

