### 3.7. Outcomes

The study’s primary endpoints are the frequencies of successful cardioversion within 6 h of drug administration as well as the combined frequency of PVCs, NSVT, SVT, bradycardia and hypotension during the same time frame. The main secondary endpoints are the frequency of patient discharges from the Emergency Department with a sinus rhythm and the frequency of successful cardioversion to a sinus rhythm within 24 h. All adverse effects, including extracardiac, will be assessed and categorized based on their severity, type and frequency. Table 3 lists all the study primary and secondary endpoints.

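### The 45% floor, the 96 per arm and the 80% power are built on a 4-hour flecainide rate, but the primary efficacy endpoint is conversion within 6 hours

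*Protocol article*

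**What the plan says.** Section 3.4 of the protocol article starts from the authors' own meta-analysis: "we estimated the pooled cardioversion rate by flecainide within 4 h 65% whereas by amiodarone 23" per cent. The Discussion also describes that meta-analysis by its result at 4 hours.

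Section 3.4 takes the 65% as point estimate and sets an acceptance rule. Flecainide passes if the lower confidence limit "does not go lower than the pooled rate (65%) by more than 20" per cent, which the text spells out as "i.e., if it is not lower than 45" per cent. From these assumptions it concludes that "a sample size of 96 patients per arm is required to achieve 80% power to demonstrate the efficacy of flecainide", "when a type I error rate is set at 0.05", and rounds up to 100 per arm.

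Section 3.7 defines the primary efficacy endpoint as "the frequencies of successful cardioversion within 6 h of drug administration". Table 3 gives the same 6-hour window, counted from drug initiation. The article gives no 6-hour conversion rate for either drug and does not justify the 4-hour rate as a proxy. Section 3.4 does not name the window to which the 45% applies.

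**The concern.** A threshold defined as a distance below a reference rate keeps its meaning only if rate and threshold refer to the same time point. Here the reference rate is cumulative conversion by 4 hours and the endpoint is cumulative conversion by 6 hours. Everyone who has converted by 4 hours has also converted by 6, so the 6-hour rate is at least as high. If the 45% is read against the 6-hour endpoint, it may lie more than 20 points below the rate that flecainide would be expected to reach by then.

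At stake is what passing the rule would mean. A drug whose 4-hour rate sits exactly at the committee's limit could pass at 6 hours more often than the confidence level implies. The power statement has the same weakness, because it describes a comparison of 4-hour rates and not the endpoint to be analysed.

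**Working it through.** **Inputs.** From section 3.4: flecainide 65% and amiodarone 23% (both within 4 h), floor 45%, 96 per arm, power 80%, type I error 0.05 (sidedness not stated), 100 per arm recruited. From section 3.7 and Table 3: 6-hour window. Assumed, because the documents give nothing: the conversion hazard between 4 and 6 hours, as a fraction f of the constant hazard over the first 4 hours.

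**Step 1: reproduce the 96.** Two-sided comparison of two proportions, pooled variance under the null, 65% v 45%, mean 0.55:

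n = [1.96·√(2·0.55·0.45) + 0.842·√(0.65·0.35 + 0.45·0.55)]² / 0.20² = (1.379 + 0.580)² / 0.04 = 95.9, so 96 per arm, with power 80.0%.

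The stated size therefore reproduces, with 45% in the place of a comparator rate. The 23% does not enter: 65% v 23% would need 21 per arm. A one-sample test of 65% against 45% would need 48.

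**Step 2: carry the rates to 6 hours.** The two extra hours are half of the first four, so

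6-hour rate = 1 − (1 − p₄)^(1 + 0.5f).

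At f = 1 the exponent is 1.5: 1 − 0.35^1.5 = 0.793 for the pooled flecainide rate, and 1 − 0.55^1.5 = 0.592 for a drug with a true 4-hour rate of 45%.

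**Step 3: chance of passing at 6 hours.** With n = 100, the Wilson lower 95% limit is 44.3% at 54 successes and 45.2% at 55, so 55 are needed. The exact (Clopper-Pearson) limit needs 56. The last two columns are binomial tail probabilities at the 6-hour rate in the column before them.

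| f (assumed) | Pooled rate at 6 h | Distance to 45% | 6-h rate if true 4-h rate is 45% | P(pass), Wilson | P(pass), exact |
|---|---|---|---|---|---|
| 0 | 65% | 20 points | 45% | 0.03 | 0.02 |
| 0.25 | 69% | 24 points | 49% | 0.13 | 0.10 |
| 0.5 | 73% | 28 points | 53% | 0.36 | 0.28 |
| 1 | 79% | 34 points | 59% | 0.83 | 0.78 |

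**Step 4: power.** With 96 per arm against a fixed 45%, an assumed 6-hour flecainide rate of 65, 70, 75 or 80% gives power of 80.0, 94.5, 99.2 or 99.9%. The stated 80% is thus exact only if nobody converts between 4 and 6 hours. If the floor moved with the rate to stay 20 points below (45, 50, 55, 60%), 96 per arm would give 80.0, 81.2, 83.3 or 86.2%.

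**Step 5: superiority over amiodarone.** With 96 per arm, power exceeds 99.9% for 65% v 23%. It also exceeds 99.9% when both rates are carried forward at f = 1 (79% v 32%). In the combinations examined (flecainide 65 to 80%), it is at least 80% when amiodarone's 6-hour rate is 20 or more points lower. It would be 55.7% for 65% v 50%, but nothing in the documents points to so narrow a gap.

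**The case against.** Several points on the other side stand.

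- **Size.** A reader might infer that the floor is much more lenient and that the real margin is 34 points. The documents do not support this. It needs the early hazard to continue unchanged to 6 hours, and section 3.6 describes a single 10-minute flecainide infusion, after which late conversions may be few. At f = 0.1 the distance is 22 points and the Wilson pass probability 0.06.
- **Direction.** That cumulative conversion cannot fall holds for one success definition in one population. Section 2 requires sinus rhythm lasting at least 1 hour, and the definition behind the pooled rate is not shown. If that hour must be completed inside the window, conversion has to occur by about 5 hours, and even a constant hazard gives 1 − 0.35^1.25 = 73%, not 79%. The trial population may also differ from the pooled one.
- **Role of the floor.** Section 2 makes superiority the efficacy goal and section 3.8 describes no test against 45%. That the floor will be applied at 6 hours is an inference. The pass probabilities above are for a one-sample rule, whereas the 96 reflects a two-group comparison.
- **Sample size.** A reader might also infer that the trial is too small. The mismatch does not show that: against a fixed 45%, a higher 6-hour rate raises power.

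These points limit the size of the problem but do not remove it. Section 3.4 still states the 45% as an acceptance rule, and it is the figure that reproduces the sample size. While it stands, it needs a time point. Its label, non-inferiority to amiodarone for a floor on flecainide's own rate, is a separate problem that this correction does not solve.

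**Conclusion.** The point holds in limited form. The floor, the 96 per arm and the 80% power all derive from a 4-hour flecainide rate, while the primary efficacy endpoint is at 6 hours, with no stated link between the two. If the fixed 45% is applied at 6 hours, it is the same as, or more lenient than, a limit 20 points below the pooled rate. The amount cannot be determined from the documents. Over the assumed range of late hazard from none to unchanged, the distance runs from 20 to 34 points, and the chance of passing for a drug truly at 45% by 4 hours runs from 0.03 to 0.83 (Wilson, n = 100). The upper ends are extreme scenarios, not estimates. All of this assumes one success definition at both time points and a floor read as a one-sample rule.

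**What to change.** Amend section 3.4 in one of two ways, before results are known:

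1. State that the 45% floor applies to cumulative conversion by 4 hours. The Holter is fitted before dosing partly to record time to cardioversion (section 3.1), so this proportion is available. Label the 80% power as referring to that 4-hour rate and give the power for the 6-hour primary endpoint separately.
2. Give 6-hour rates for both drugs with their source, then restate the floor and the power for the 6-hour primary endpoint.

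Either way, keep n = 200. The cost is wording, one extra Holter-derived proportion under the first option, and under the second a floor that may be less favourable to flecainide. No extra patients are needed.

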## 2. Objectives

The primary goals of this clinical trial are to prove the superiority of flecainide over amiodarone in the successful cardioversion of paroxysmal atrial fibrillation at the Emergency Department and to prove that the safety of flecainide is non-inferior to amiodarone in patients with coronary artery disease without residual ischemia and an ejection fraction over 35%. The secondary goals of the study are to prove the superiority of flecainide over amiodarone in the reduction in hospitalizations from the Emergency Department due to atrial fibrillation in the time taken to achieve cardioversion, and in the reduction in the need to conduct electrical cardioversion. A successful cardioversion is defined as the restoration of the sinus rhythm, documented by a 12 lead ECG lasting at least 1 h. 

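### The efficacy criterion in the sample-size section contradicts the superiority objective: it judges flecainide against a fixed 45%, uses no amiodarone data, and does not match the stated 96 per arm

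*Protocol article*

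**What the plan says.** **Objective.** Section 2 states: "The primary goals of this clinical trial are to prove the superiority of flecainide over amiodarone in the successful cardioversion". The same sentence applies non-inferiority to safety only, and the Abstract says the same.

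**Endpoint.** Section 3.7 reads: "primary endpoints are the frequencies of successful cardioversion within". The window named there is 6 hours, and a combined safety frequency is the other primary endpoint. Table 3 gives the same 6-hour window.

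**Criterion.** Section 3.4 starts from a meta-analysis: "we estimated the pooled cardioversion rate by flecainide within 4 h 65% whereas by amiodarone 23" percent. The conclusion it wants to reach is worded as follows: "flecainide can be regarded as non-inferior to amiodarone in patients with ischemic cardiomyopathy". The condition attached to that conclusion is a limit on an interval for flecainide: "if the lower margin of the confidence interval does not go lower than the pooled rate (65%) by more than 20" percent. A parenthesis then turns the condition into an absolute figure: "i.e., if it is not lower than 45" percent.

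**Sample size.** From this, section 3.4 concludes that "a sample size of 96 patients per arm is required to achieve 80% power to demonstrate the efficacy of flecainide in these patients". The error rate comes in a separate clause, with no word on whether it is one- or two-sided: "when a type I error rate is set at 0.05". The target is rounded up to 100 per arm.

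**The concern.** One primary endpoint carries two different hypotheses. The Objectives ask whether flecainide converts more patients than amiodarone. Section 3.4 asks whether flecainide's own rate is credibly at or above 45%, and labels a positive answer non-inferiority to amiodarone.

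The 45% is 65% − 20 points, and the 65% is flecainide's historical rate. The amiodarone figure of 23% is quoted but does not enter the criterion. Nor does the result of the concurrent amiodarone arm. A statement about flecainide relative to amiodarone cannot rest on a rule with only flecainide in it.

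The reference rate is also a 4-hour rate, while the endpoint is counted to 6 hours.

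At stake is which result counts as success. The trial is open-label (section 3.3). With two success criteria on the page, the choice between them could be made after the results are known.

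**Working it through.** **Inputs.** From section 3.4: flecainide 65%, amiodarone 23% (both pooled, 4 h), threshold 45%, 80% power, error rate 0.05, 96 per arm, 100 per arm recruited. Two-sided 0.05 is inferred from step 1. Normal quantiles: 1.960 and 0.842.

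**1. Reproducing the 96.** Two-sample comparison of proportions with pooled variance under the null:

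n per arm = [1.960·√(2p̄(1−p̄)) + 0.842·√(p₁(1−p₁) + p₂(1−p₂))]² / (p₁−p₂)²

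With p₁ = 0.65, p₂ = 0.45, p̄ = 0.55: [1.960 × 0.7036 + 0.842 × 0.6892]² / 0.20² = 95.9, so **96 per arm**, power 80.0%. The calculation therefore treats 45% as the rate in a second arm. Other versions do not give 96:

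| Calculation | n |
|---|---|
| 65% vs 45%, one-sided 0.05 | 76 per arm |
| 65% vs 45%, continuity-corrected | 106 per arm |
| Two-arm non-inferiority, 65% in both arms, 20-point margin, one-sided 0.025 | 90 per arm |
| Same, one-sided 0.05 | 71 per arm |

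The unpooled version of 65% vs 45% gives 94, the same test in a slightly different form.

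**2. The size the written rule needs.** One sample, true rate 65%, fixed bar 45%, two-sided 0.05:

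- null variance for the error-rate term: [(1.960·√(0.45 × 0.55) + 0.842·√(0.65 × 0.35)) / 0.20]² = 47.4, so 48
- variance at 65% throughout: (1.960 + 0.842)² × 0.65 × 0.35 / 0.20² = 44.6, so 45

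That is **about 45–48 flecainide patients**, with no control arm in the calculation.

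**3. The size the stated objective needs at the quoted rates.** The formula of step 1 with 0.65, 0.23 and p̄ = 0.44: [1.960 × 0.7020 + 0.842 × 0.6361]² / 0.42² = 20.7, so **21 per arm** (26 with continuity correction).

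**4. How the written rule behaves with 100 flecainide patients.** The smallest count whose 95% lower limit reaches 45% is 55 (Wald limit 0.4525, Wilson 0.4524) or 56 (exact limit 0.4572; at 55 it is 0.4473). Binomial probabilities of passing:

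| True flecainide rate | P(X ≥ 56) | P(X ≥ 55) |
|---|---|---|
| 50% | 0.136 | 0.184 |
| 58% | 0.695 | 0.762 |
| 65% | 0.975 | 0.985 |

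No amiodarone rate appears in the table because none enters the rule.

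- *Assumed 50% vs 25%.* The rule fails with probability 1 − 0.184 = 0.82 to 1 − 0.136 = 0.86. A two-arm superiority test with 100 per arm has power Φ[(0.25 × 10 − 1.960 × 0.6847) / 0.6614] = 0.96.
- *Hypothetical 58% vs 78%.* The rule passes 70–76% of the time, although flecainide is 20 points worse. A two-arm test with a 20-point margin would pass 2.5% of the time, by construction, because the case sits on the margin.

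**5. Superiority power at 100 per arm, flecainide 65%.** The amiodarone rates above 23% are assumptions.

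| Amiodarone rate | Power, two-sided 0.05 |
|---|---|
| 23% | >99.9% |
| 40% | 95% |
| 45% | 82% |
| 50% | 57% |

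Section 3.8 sets p = 0.03 for the final analysis if there is an interim look. The quantile then becomes 2.170, and the 45% row becomes Φ[(0.20 × 10 − 2.170 × 0.7036) / 0.6892] = 75%.

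**The case against.** The best defence is that section 3.4 is a garbled account of a two-arm calculation. Step 1 supports this: 96 comes out exactly when 45% is a comparator rate. On that view nobody intended a single-arm decision rule. This is plausible, but it does not rescue the text. The section says when the steering committee would regard flecainide as non-inferior, and the absolute 45% rules out reading the interval as one for a between-arm difference. If 45% was meant as the comparator's rate, it conflicts with the 23% quoted in the same section.

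A reader might infer that the trial never uses its amiodarone arm and never tests superiority. The document does not support that. Section 2 sets superiority as a goal, section 3.1 describes a randomised head-to-head comparison, and section 3.8 covers all primary endpoints without adopting the 45% rule. The article names no between-arm test, but the full protocol or analysis plan, not shown, may do so. The defect is confined to the criterion in section 3.4.

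A reader might also infer that the trial is too small. At the quoted rates it is not: power exceeds 99.9%. At those rates the rule also passes 97.5–98.5% of the time, so the two criteria would nearly always agree. They diverge when flecainide does worse than 65%, or amiodarone much better than 23%. The 78% amiodarone case is far from the documented rate and only shows that the rule ignores the comparator.

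Finally, it is tempting to say that a 4-hour reference makes a 6-hour bar easier. More time allows more conversions, but the trial requires sinus rhythm for at least 1 h and enrols only coronary patients. Whether the pooled rate used a similar definition or population is not shown. The mismatch stands; its net direction is unproven.

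**Conclusion.** The point holds as a contradiction within the article. Hypothesis, criterion and sample size describe three different tests: two-arm superiority, one sample against 45%, and two samples at 65% against 45%. The criterion as written cannot support any statement about flecainide relative to amiodarone.

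The more relevant error is wrongly failing a better drug: 82–86% failure at 50% against 25%, where superiority would be shown with 96% power. Both rates are assumed, with 25% close to the documented 23%. Wrongly passing a worse drug is possible in principle, but the illustration needs an amiodarone rate that the document does not suggest. The figures assume 100 evaluable patients per arm and two-sided 95% limits. The point must be fixed before analysis because it determines what counts as success on a primary endpoint.

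**What to change.** Replace the 45% criterion in section 3.4 with: *Primary efficacy: difference in the proportion converted within 6 h (flecainide minus amiodarone) in all randomised patients; superiority is concluded if the two-sided confidence interval lies above 0.* Set the interval at 95%, or at 97% to match p = 0.03 if an interim analysis is done, so that the sentence agrees with section 3.8. Use the word non-inferiority only for the safety endpoint.

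Removing the 45% rule also removes the only basis for 96 per arm, so the size needs a new justification. Keep 200 patients and state the size as a two-arm superiority calculation, for example about 82% power at 100 per arm for 65% against an assumed amiodarone rate of 45% (about 75% at the 0.03 level), and more than 99.9% for 65% against 23%. Say that the 45% is an assumption and that the planning rates are 4-hour rates applied to a 6-hour endpoint.

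The cost is a wording amendment and a short recalculation in the protocol, carried into the analysis plan. Recruitment, treatment and data collection do not change.

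### The stated 96 per arm for 80% power does not follow from the stated rates or the stated non-inferiority rule; it matches superiority of 65% over 45%, and 45% is never given as an amiodarone rate

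*Protocol article*

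**What the plan says.** Section 3.4 (Sample Size) starts from a meta-analysis: "we estimated the pooled cardioversion rate by flecainide within 4 h 65% whereas by amiodarone 23" per cent. It then calls flecainide non-inferior to amiodarone "if the lower margin of the confidence interval does not go lower than the pooled rate (65%) by more than 20" percentage points, explained as "i.e., if it is not lower than 45" per cent. On that basis it says: "we expect that a sample size of 96 patients per arm is required to achieve 80% power to demonstrate the efficacy of flecainide", with the qualifier "when a type I error rate is set at 0.05". The sidedness of that error rate is not given. The 96 is rounded up to 100 per arm, 200 in total. Section 3.3 sets a 1:1 allocation.

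Three other places bear on this:
- Section 2 (Objectives) makes superiority the aim for cardioversion and non-inferiority the aim for safety.
- Section 3.7 and Table 3 measure primary cardioversion over 6 hours, not 4.
- Section 3.8 sets a final significance threshold of 0.03 if an interim analysis is held.

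**The concern.** The paragraph prints its rates, its decision rule, its power, its type I error and its result, so the result can be checked against the inputs. Three things do not fit together.

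1. The non-inferiority rule concerns the cardioversion rate, for which Section 2 claims superiority.
2. The rule's floor of 45% is 65% minus 20 points. It is not tied to amiodarone, whose only stated rate ("whereas by amiodarone 23" per cent) lies 22 points below the floor.
3. The number 96 is presented as following from these assumptions.

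If 96 follows from none of them, a reader cannot tell which hypothesis has 80% power, or under which amiodarone rate. The planned power is then tied to a control rate that the reader is not shown. That matters most if an interim analysis is held, because the stricter final threshold lowers power under that rate.

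**Working it through.** **Inputs.** From Section 3.4: 65%, 23%, the 20-point margin with its 45% floor, power 80%, type I error 0.05. From Section 3.3: 1:1 allocation. Sidedness is not stated, so both are shown where it matters. Normal quantiles: 1.960 (two-sided 0.05 or one-sided 0.025), 1.645 (one-sided 0.05), 0.8416 (80% power).

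**Step 1: a calculation that reproduces 96.** Two-proportion superiority with pooled variance under the null, where p̄ is the mean of the two rates:

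n per arm = [z_α √(2p̄(1−p̄)) + z_β √(p1(1−p1) + p2(1−p2))]² / (p1−p2)²

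With 65% and 45%, p̄ = 0.55, and the roots are 0.7036 and 0.6892:

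n = (1.960×0.7036 + 0.8416×0.6892)² / 0.20² = 1.959² / 0.04 = 95.9, so 96. Power at 96 is 80.0%. The arcsine version gives 95.8 and the unpooled version 93.2.

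**Step 2: superiority at the stated rates.** With 65% and 23%, p̄ = 0.44, and the roots are 0.7020 and 0.6361:

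n = (1.960×0.7020 + 0.8416×0.6361)² / 0.42² = 1.911² / 0.1764 = 20.7, so 21 per arm. With continuity correction it is 26. Fisher's exact test needs about 24 to 25. In total, 42 is about a fifth of 200. Power at 96 or 100 per arm is above 99.9%.

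**Step 3: two-arm non-inferiority, both rates 65%, margin 20 points.**

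n = 2×0.65×0.35×(z_α + z_β)² / 0.20²

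- One-sided 0.025: 0.455×7.849 / 0.04 = 89.3, so 90.
- One-sided 0.05: 0.455×6.183 / 0.04 = 70.3, so 71.

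Power at 96: the standardised margin is 0.20 / √(0.455/96) = 2.905. Subtracting 1.960 gives 0.945, or 83%. Subtracting 1.645 gives 1.260, or 90%. If the true rates are 65% and 23%, non-inferiority needs only 9 or 7 per arm.

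**Step 4: the rule taken literally.** The lower limit of the flecainide rate is compared with a fixed 45%, at two-sided 0.05:

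n = (1.960×√(0.45×0.55) + 0.8416×√(0.65×0.35))² / 0.20² = 47.4. With the variance taken at 65% throughout, n = 44.6. The exact binomial test needs 50. These are flecainide patients only. Power at 96 is about 97%.

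| Reading | Patients for 80% power |
|---|---|
| Superiority, 65% vs 23% | 21 per arm (24–26 exact or corrected) |
| Non-inferiority, 65%/65%, 20 points | 90 or 71 per arm |
| Non-inferiority, true 65% vs 23% | 9 or 7 per arm |
| Flecainide limit against a fixed 45% | 45–50 flecainide patients |
| Superiority, 65% vs 45% | 96 per arm |

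**Step 5: power at 100 per arm for 65% vs 45%.** Power = Φ[(0.20×√100 − z_α×0.7036) / 0.6892].

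- At two-sided 0.05: (2 − 1.379) / 0.6892 = 0.901, or 82%.
- At two-sided 0.03 (z = 2.170): (2 − 1.527) / 0.6892 = 0.687, or 75%.
- For comparison, 65% vs 23% stays above 99.9% at either threshold.

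**The case against.** The strongest reply is that nothing was miscalculated. The figures 65%, 45%, 0.05 and 80% are all printed in the paragraph and together give exactly 96. The paragraph names no formula, test or software, and a condensed article may leave those to the full protocol. Other calculations also come close. An equivalence test at 65%/65%, and one-sided 0.05 non-inferiority at 90% power, each give 98. Continuity-corrected non-inferiority at one-sided 0.025 gives 99.03, so 100.

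Part of this stands. How 96 arose is an inference: 45% may have been a floor carried over, or a cautious control rate left unlabelled. The near misses do not rescue the text, because it describes no equivalence test, states 80% power rather than 90%, and gives 96 rather than 100. Leaving details to a full protocol does not help either, since the inputs and the result that disagree are all printed here.

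Two stronger readings are tempting and are not supported.

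- A reader might infer that the trial is underpowered for efficacy, or much too large. At the stated rates it is well powered. It cannot be called too large on efficacy alone, because safety is also a primary endpoint and the 6-hour amiodarone rate may differ from 23%.
- A reader might infer that safety was never sized. The article gives no safety event rate or margin, and the full protocol is not shown, so this cannot be concluded from the paragraph.

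**Conclusion.** The point holds in a limited form. The stated 96 per arm for 80% power follows neither from the stated rates nor from the stated non-inferiority rule. It corresponds to two-sided superiority of 65% over 45%, and 45% is not given anywhere as an amiodarone rate. The rule also conflicts with the superiority objective in Section 2, and the planning rates are for 4 hours while the endpoint is at 6.

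The consequence for the efficacy result is small. With 100 per arm, power is above 99.9% if 65% and 23% apply at 6 hours, and 82% if amiodarone converts 45%. It falls below the 80% target, to about 75%, only if the 45% rate holds, an interim analysis takes place and the final test uses 0.03. These figures assume normal approximations, two-sided tests, 1:1 allocation and no dropout. The 6-hour amiodarone rate is not given, so the 23% to 45% range is an assumption built from figures printed in the paragraph.

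Severity: should-fix. The justification is incoherent and needs restating, but the planned size does not threaten the efficacy comparison at the stated rates.

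**What to change.** Keep 200 patients and rewrite the sample-size paragraph:

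1. Remove the non-inferiority sentence from the efficacy sizing, or reconcile it with Section 2.
2. Name the efficacy hypothesis as superiority at two-sided 0.05.
3. State and justify the assumed amiodarone rate at 6 hours, and say that the meta-analytic rates are 4-hour rates. If 45% is meant as a cautious 6-hour rate, say so.
4. Restate power, for example: With 100 patients per arm and a two-sided 0.05 test, power for superiority in cardioversion by 6 hours exceeds 99.9% at 65% vs 23% and is 82% at 65% vs 45%; if an interim analysis is held and the final test uses 0.03, the latter is about 75%.

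The cost is one rewritten paragraph and a slightly less favourable stated power if an interim analysis is held. Recruitment and trial conduct do not change.
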